**Methods:**

The goal is to recruit up to 1150 patients at baseline in five rehabilitation centers across Germany. For ethical reasons, partially randomized experimental study design is used to quantitatively assess the effectiveness of web-based aftercare programs. All patients are offered the traditional face-to-face aftercare treatment (IRENA). When patients deny to participate in traditional face-to-face aftercare, they are randomly distributed into either web-based aftercare (digIRENA) or a control group. In all three groups, the SF-12, which measures subjective health, and the WAI, which measures working ability, will be used at baseline, 13 weeks, 26 weeks and 43 weeks after the patients have left the rehabilitation center. BREQ-2, which measures motivation, is used only in the traditional aftercare group and the web-based aftercare group. A multivariate analysis of variance with repeated measurement and latent growth curve models will be used to compare the development of the variables in the three groups. For the qualitative part of the study, interviews with patients and therapists will be conducted to shed light on the applicability, acceptance, and usability of web-based aftercare programs.

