#### Data collection of quantitative study

The data collection started in January 2020. Due to the pandemic, the rehabilitation centers did not receive any patients from mid-March until about mid-May. To increase the number of recruited patients, two more rehabilitation centers joined the project in August 2020 (initially there were only three centers). The recruitment of the patients is planned to finish in October 2021. In total, the data collection includes four measurement occasions. The baseline measurement takes place at the rehabilitation center before the start of the intervention, the first follow-up measurement 13 weeks after the baseline, the second follow-up 26 weeks after the baseline, and the third follow-up 43 weeks after the baseline (see Fig. 2). The first three measurement occasions represent the development of the outcome variables, approximately, before, during and at the end of the intervention. Due to the limited duration of the study, the last follow-up measurement is intended to illustrate the sustainability of developments over the next 4 months. For the measurements 2–4, the questionnaires are directly sent to the patients, in accordance to their preference via post or e-mail. A reminder is sent in case the patients have not returned the questionnaires after 2 weeks.

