#### Data analysis of quantitative data

Data are entered by research assistants and checked for accuracy by an independent research assistant. All personal information is pseudo-anonymized. Missing data are treated using either the multiple imputation or the full-information maximum likelihood approach. A first analysis will include all patients who intended to participate in the interventions and a second study will include only those patients who actually completed the interventions. A multivariate analysis of variance with repeated measurements will be used to analyze the data. Additionally, the development of work ability and subjective health will be analyzed by latent growth curve models [32]. These models allow the analysis of linear and nonlinear developments over time. A mediation analysis will be conducted to test whether motivation mediates the effects of the intervention on the attendance rate. The effects of age and gender will be controlled.

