## Discussion

The purposes of this study are 1) to assess the efficacy of a web-based platform used in the aftercare of a rehabilitation stay whilst looking at 1a) attendance, 1b) work ability, 1c) subjective health and 1d) motivation as well as 2) to gain deeper insights into how a web-based platform is perceived by therapists and patients whilst looking at 2a) applicability, 2b) acceptance and 2c) usability.

Due to an increased proportion of aging population in Germany, web-based rehabilitation aftercare could be an effective supplement to the traditional face-to-face rehabilitation aftercare. It has the potential to reach those people who cannot easily reach and not have access to traditional face-to-face rehabilitation aftercare. As traditional face-to-face rehabilitation aftercare suffers from low level of usage due to inflexible offers in terms of time and long distances to rehabilitation centers, web-based aftercare could help tackle some of these problems.

This study has several strengths and limitations. A strength of this study is the design as a partially randomized control trial, which enables us to draw strong conclusions about the effectiveness of the intervention. Additionally, the intended sample of the study is large enough to find even small effects. Furthermore, the longitudinal structure of the study enables us to examine development trajectories in the outcome variables. Finally, we use reliable and valid measures of the outcome variables, which have been tested in a vast amount of studies.

A limitation is that the corona pandemic partially interrupted the course of the study so that we lost a part of the participants due to this interruption. Therefore, we requested to include additional clinics and to prolong the duration of the study to reach the aimed number of participants. It is possible that the interruption could influence the results of the study.

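### Comparisons with the self-selected IRENA group are adjusted, as far as the article says, for age and gender, leaving centre and enrolment period as possible confounders

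*Protocol article*

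**What the plan says.** The protocol article's section on sampling and participants offers IRENA to everyone first and randomises only the decliners, 1:1 by sealed envelope, to digIRENA or control. It mentions no stratification by centre.

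The section on data collection of the quantitative study gives the calendar: "The data collection started in January 2020"; "Due to the pandemic, the rehabilitation centers did not receive any patients from mid-March until about mid-May"; "two more rehabilitation centers joined the project in August 2020 (initially there were only three centers"; and "The recruitment of the patients is planned to finish in October 2021". Follow-up is at 13, 26 and 43 weeks after baseline.

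The section on data analysis of quantitative data states: "A multivariate analysis of variance with repeated measurements will be used to analyze the data". It adds growth-curve models for work ability and subjective health, then a mediation analysis, and closes with the covariate sentence: "The effects of age and gender will be controlled". The abstract makes clear that all three arms are compared: "latent growth curve models will be used to compare the development of the variables in the three groups".

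The Discussion says of the closure: "It is possible that the interruption could influence the results of the study". The article links no analysis step to that remark.

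**The concern.** Because IRENA membership follows patient choice, the IRENA share may differ between centres and between stages of the pandemic. If recovery after rehabilitation also differs along those lines, the IRENA group and the two randomised groups are different mixtures of centres and periods. Part of that difference in mixture would then appear as a difference in development between programmes. Adjusting for age and gender does not deal with this.

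The article is not silent on adjustment. It names two covariates, and it was written when the closure and the added centres were already known. Centre and baseline date should be known for every patient, since baseline is taken at the centre. What is at stake is how the IRENA-digIRENA and IRENA-control comparisons can be read, and whether the Discussion's remark about the closure can be examined at all.

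**Working it through.** The plan gives no figure on this point to reproduce. The steps below use its calendar; uptake and centre effects are assumptions, because the article gives neither.

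**1. Exposure by centre and period**, in open centre-months, with August 2020 and October 2021 counted as full months:

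- January to mid-March 2020: 3 centres × 2.5 = 7.5
- mid-May to July 2020: 3 × 2.5 = 7.5
- August 2020 to October 2021: 5 × 15 = 75
- total: 90

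Assuming equal accrual per centre-month, the added centres supply 2 × 15 / 90 = 33% of patients and the pre-closure cohort 7.5 / 90 = 8%. Other readings of the joining and closing months give 31–33% and 8–9%. If the added centres recruit at half to twice the rate of the others, the shares are about 19–50% and 6–11%.

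**2. Timing of the first cohort.** Counted from baseline, 13 weeks after early January is early April 2020, and 13 weeks after mid-March is mid-June 2020. Patients enrolled before about mid-February (roughly 1.5 of the 2.5 months) reach week 13 while the centres were receiving no patients. The rest reach it in the month after reopening. Everyone enrolled later has all four occasions after reopening.

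**3. Bias in an IRENA comparison.** Let 60 and 30 be the centre-months of the initial and added centres, u₁ and u₂ the IRENA uptake in each, and d the difference in change between added and initial centres. Then

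- added-centre share in IRENA = 30u₂ / (30u₂ + 60u₁)
- added-centre share in the randomised groups = 30(1−u₂) / (30(1−u₂) + 60(1−u₁))
- bias = d × (first share − second share)

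With d = 0.3 SD (assumed):

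| Uptake, initial / added centres | Share in IRENA | Share in randomised groups | Bias |
|---|---|---|---|
| equal | 33% | 33% | 0 |
| 30% / 40% | 12/30 = 40% | 18/60 = 30% | 0.03 SD |
| 20% / 35% | 10.5/22.5 = 47% | 19.5/67.5 = 29% | 0.05 SD |
| 20% / 50% | 15/27 = 56% | 15/63 = 24% | 0.10 SD |
| 40% / 20% | 6/30 = 20% | 24/60 = 40% | −0.06 SD |

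The sign depends on where uptake is higher. The bias is proportional to d.

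**4. The same calculation for enrolment period**, with 7.5 pre-closure and 82.5 later centre-months and d = 0.3 SD:

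- Uptake 50% before, 20% after: 3.75/20.25 − 3.75/69.75 = 0.185 − 0.054 = 0.131, a bias of 0.04 SD.
- Uptake 35% before, 20% after: 2.625/19.125 − 4.875/70.875 = 0.137 − 0.069 = 0.068, a bias of 0.02 SD.

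**5. Scale.** With the planned 573 split equally, 573 / 3 = 191 per group, and the standard error of a two-group difference in change is √(2/191) = 0.10 SD of change. A bias of 0.10 SD is therefore about one standard error; 0.03 SD is about a third of one.

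**6. digIRENA against control.** Both groups are drawn concurrently from the same decliners. If 1:1 allocation held within centre and period, their centre and period mix is equal in expectation and the bias is 0.

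**The case against.** The strongest reply is that this is a condensed article. It nowhere says that centres and periods are pooled, or that age and gender are the only covariates. Centre terms and pandemic sensitivity analyses may stand in an analysis plan that is not shown. The covariate sentence also follows directly on the mediation analysis and may refer only to that. A reader might infer that the sponsor has decided to leave centre out; the text does not support that. What remains is that the article does name a covariate set, and that set lacks the two variables its own account of recruitment makes relevant. If the sentence covers only the mediation analysis, the main models have no named covariate.

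Other points on that side also stand:

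- A constant difference in level between centres cancels in a group-by-time comparison. Only differences in change matter, and only together with unequal uptake. The documents show neither.
- A reader might take the first cohort's change from baseline to week 13 as running from before to after the closure. By the article's dates, more than half of that enrolment window reaches week 13 during it.
- A reader might extend the bias to the randomised contrast. Random allocation rules that out in expectation, subject to the condition in step 6.
- IRENA comparisons are observational by design. Centre and period are only part of their confounding.

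**Conclusion.** The concern holds for comparisons of IRENA with digIRENA or control, and only there. Centre and enrolment period are plausible confounders that the stated covariates do not address, and the closure effect the article concedes has no analysis attached to it. The size is unknown. Over the cases shown it is 0 to about 0.10 SD for centre and 0.02 to 0.04 SD for period. These figures rest on equal accrual per centre-month, assumed uptake gaps and an assumed 0.3 SD difference in change; they are not estimates of the bias in this trial. For digIRENA against control, leaving the two variables out mainly costs precision.

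**What to change.** In the section on data analysis of quantitative data, state that the repeated-measures and growth-curve models include, besides age and gender, centre (five levels) and enrolment period (baseline before mid-March 2020 against after reopening), each with its interaction with time. Make clear that the covariate sentence covers these models as well as the mediation analysis. Repeat the IRENA comparisons restricted to patients enrolled after reopening, and refer to that analysis where the Discussion raises the interruption.

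The cost is 4 + 1 = 5 extra parameters per occasion, in a planned 573 patients, and one more table. No new data or patients are needed. Two limits should be stated with it: the period effect is estimable only from the three initial centres, and one category for all enrolment after reopening leaves any later drift unadjusted. The IRENA comparisons remain non-randomised after adjustment and should be reported as such.

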#### Sampling and participants

Patients with orthopedic complaints who have applied for and been approved for rehabilitation on the prescription of a primary care physician are recruited from five rehabilitation centers throughout Germany. The inclusion criteria are that patients are at least 18 years old, have a basic knowledge of the German language, and their primary diagnosis concerns an orthopaedic problem. Furthermore, only patients who are insured with the public pension insurance Knappschaft Bahn See can participate in the study, as the included rehabilitation centres belong to Knappschaft Bahn See. When patients are informed about the possibility to take part in an aftercare program during their stay, they are also asked to participate in the study. In case they give their consent, they are assigned to three groups: (1) traditional face-to-face aftercare program (IRENA), (2) web-based aftercare program (digIRENA), or a control group. For ethical reasons, a partial randomized controlled trial was used. All patients are first asked whether they want to take part in the traditional aftercare program (IRENA). Only if they deny, they are randomly assigned to the web-based aftercare program or the control group. This means that the IRENA condition was offered preferentially and the randomization referred only to the digIRENA and control condition. Sealed envelops are used for the randomization and patients only know their group after opening the envelop. The envelops are distributed with the goal to obtain a ratio of 1:1 between the two groups. Due to nature of the study neither participants nor staff can be blinded to allocation. As an incentive to take part in the study, all patients who complete the study with all measurement occasions receive a 50 Euro Amazon voucher.

Because only a small number of studies exists in relation to web-based aftercare interventions, we chose to take a conservative approach in the power analysis with a small estimated effect size [8]. Conservatively estimating the effect size by Cohen’s *f* = .15, *α* = .05, 1-*β* = .80, with three groups, a correlation among repeated measures of *r* = .30 and a design with three repeated measurement occasions, on average, using an ANOVA with repeated measures (within-between interaction), the calculated total sample size is 573 participants, nearly equally distributed over three groups. Since we expect a dropout rate of about 50% [25], the plan is to recruit 1150 patients.

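### The stated and powered three-group test can be significant with no digIRENA effect, because only digIRENA versus control is randomised and no passage makes that contrast the test of effectiveness

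*Protocol article*

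**What the plan says.** **Allocation.** Under Sampling and participants, every consenting patient is offered IRENA first. "Only if they deny, they are randomly assigned to the web-based aftercare program or the control group" The section is explicit that "the randomization referred only to the digIRENA and control condition", with envelopes distributed "to obtain a ratio of 1:1 between the two groups".

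**Analysis.** The Abstract (Methods) says that repeated-measures MANOVA and latent growth curve models "will be used to compare the development of the variables in the three groups". Data analysis of quantitative data repeats the two methods and names no contrast between particular groups. After a sentence on mediation it adds: "The effects of age and gender will be controlled".

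**Sample size.** The calculation under Sampling and participants is for a within-between interaction with three groups of nearly equal size, 573 analysed patients in total.

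**Claim.** The Discussion lists as a strength the design as a "partially randomized control trial, which enables us to draw strong conclusions about the effectiveness of the intervention". It does not restrict this to the randomised pair, and its limitations paragraph does not mention self-selection into IRENA.

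**The concern.** Of the three pairwise comparisons, one is randomised. The other two set patients who accepted face-to-face aftercare against patients who declined it. The Background gives two reasons for not attending: lack of time after returning to work, and distance. Return to work is closely tied to work ability, which is an outcome, so choosers and decliners may well follow different courses whatever aftercare they receive.

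The three-group interaction asks whether any group's course differs from the others. It does not ask whether digIRENA patients do better than controls. If it is significant because IRENA alone diverges, it says nothing about the web-based programme. The document fixes this test, powers the trial on it and describes the design as supporting strong conclusions. The randomised contrast, which does answer the effectiveness question for work ability and subjective health, is given no special place.

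**Working it through.** **1. The plan's own figure.** The stated inputs are f = 0.15, α = 0.05, power 0.80, k = 3 groups, m = 3 occasions and r = 0.30. The usual noncentral F calculation for the within-between interaction is

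λ = f²·N·m/(1 − r), df1 = (k − 1)(m − 1) = 4, df2 = (N − k)(m − 1).

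At N = 127, λ = 0.0225 × 127 × 3/0.70 = 12.25 and power is 0.80. The formula therefore gives 127 patients (129 with equal groups), not 573. None of the variants of the stated test that were tried gives 573. That is a separate matter. Here 573 is taken as the analysed size because the protocol states it. The recruitment target follows from it: 573/(1 − 0.50) = 1146, rounded to 1150.

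**2. The three-group test when digIRENA does nothing.** Let digIRENA and control have identical means on all occasions. Let IRENA diverge linearly: 0, d/2, d (in SD) at occasions 1, 2, 3. Centred over time this is −d/2, 0, d/2, with sum of squares d²/2. If IRENA is a fraction p of the sample,

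λ = N·p(1 − p)·(d²/2)/(1 − r).

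- Equal groups (p = 1/3): λ = 573 × 0.2222 × 0.5/0.70 × d² = 90.95·d².
- IRENA at 15% (p = 0.15): λ = 573 × 0.1275 × 0.5/0.70 × d² = 52.18·d².

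With df1 = 4 and df2 = 1140, the probability of rejection at α = 0.05 is:

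| d (assumed) | λ, equal groups | rejects | λ, 15% IRENA | rejects |
|---|---|---|---|---|
| 0.1 | 0.91 | 10% | 0.52 | 8% |
| 0.2 | 3.64 | 29% | 2.09 | 18% |
| 0.3 | 8.19 | 61% | 4.70 | 37% |
| 0.4 | 14.55 | 88% | 8.35 | 62% |

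The documents give neither d nor the 15% share; both are assumptions. The Background's figure of under 15% is general participation in aftercare, whereas the sample-size section plans nearly equal groups.

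**3. Checks.** Simulation with 191 per group and compound symmetry at r = 0.30 (4000 runs per point) gave 10%, 29%, 60% and 87% for the four values of d. In the same runs the interaction test on digIRENA and control alone rejected in 4–6%, whatever IRENA did. The trial has four occasions. With linear drift to d at the fourth, equally spaced for simplicity, the formula gives 9%, 27%, 59% and 87% with equal groups, and 7%, 16%, 35% and 60% at 15% IRENA.

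**4. Is the randomised contrast workable?** For two groups, f = 0.15 corresponds to d = 2f = 0.30. That needs about 175 per arm for 80% power (two-sided α = 0.05). The planned 573/3 = 191 per arm give 83% on a single post-treatment score, 87% with baseline-adjusted ANCOVA at r = 0.30, and 70% on a simple change score.

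**The case against.** The partial randomisation is disclosed openly. A three-group growth model would ordinarily estimate each group's course, including digIRENA against control, and follow-up contrasts are commonly left to an analysis plan that is not shown. All this is fair, and it limits how far the point can be pressed. A reader might infer more than the document supports:

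- *That a selection effect will be reported as a digIRENA effect.* No passage says so. What stands is that the named and powered test permits it and the Discussion claim does not guard against it.
- *That randomised and self-selected patients are pooled.* No arms are merged; they share one overall test.
- *That adjustment is for age and gender alone.* The text does not say only, and the sentence follows the mediation analysis, so it may not cover the main comparison. The randomised contrast needs no confounder adjustment in any case.
- *That baseline imbalance drives the result.* Baseline is one of the occasions, so a constant difference in level produces no group-by-time effect. Differing trajectories do.
- *That the Discussion claims strong conclusions about IRENA.* The intervention there can be read as digIRENA. The sentence still does not say which comparison carries the claim.
- *That digIRENA versus control answers every aim.* Attendance at the programme and motivation are not assessed in controls (Measures), so those aims rest on IRENA versus digIRENA, which is not randomised.

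The calculation also cannot tell selection from a true IRENA benefit, and it uses the univariate interaction test of the sample-size section rather than the MANOVA. Neither changes the conclusion: in both cases a significant result is uninformative about digIRENA.

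**Conclusion.** The point holds in this form: the three-group interaction on which the trial is sized can be significant with digIRENA identical to control, and the protocol neither designates the randomised contrast as the test of effectiveness nor limits its claim to it. Under assumed IRENA divergence of 0.1 to 0.4 SD, the chance of such a result runs from about 10% to 88% with equal groups and from about 8% to 62% with IRENA at an assumed 15%. These figures rest on N = 573, r = 0.30, three occasions, compound symmetry and linear divergence. The exact percentages depend on those assumptions; the mechanism does not. The valid comparison is already in the design and is reasonably powered at d = 0.30 if 191 per randomised arm are analysed. The defect is therefore in the stated inference and not in the data to be collected.

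**What to change.** 1. For work ability (WAI) and subjective health (SF-12), name digIRENA versus control among randomised patients, analysed as randomised, as the confirmatory group-by-time contrast.
2. Report every IRENA comparison as observational. This includes attendance and motivation, which are available only for IRENA versus digIRENA. Adjust for baseline WAI and SF-12, age, gender and centre, adding baseline BREQ-2 only for IRENA versus digIRENA because controls do not complete it.
3. State that confounding by return to work and distance may remain. The article does not describe either as a collected covariate, so the adjustment above does not remove it.
4. In the Discussion, limit the sentence on strong conclusions to digIRENA versus control in patients who decline IRENA.

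The cost is a change of wording and a few covariates from data already planned. The downside is that claims about IRENA, including how digIRENA compares with it, become weaker.
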